### Ethical consideration

Ethical approval to conduct the study has been obtained from the Human Research Ethics Committee of the University of Newcastle in Australia (reference number H-2021-0414) and the ethics committee of the study venue (reference number B2021-096R). Patients will be informed that participation is voluntary and that they can withdraw at any time without a reason. The trial will be discontinued for a given participant if the participant withdraws consent, or if the participant develops a condition that has been diagnosed by the clinical practitioner as unsuitable for continuing the rehabilitation programme, such as joint dislocation and severe fall. The conditions would be documented as adverse events and would be reported to the hospital for evaluation and treatment. Identification codes will be used in data collection to ensure participants’ privacy and anonymity. All electronic data will be saved in a password-protected cloud system of the university. The non-digital documentation will be stored in a locked cabinet in the researcher’s office. Data collected in this study will only be accessed by the research team members. Ethics committees at the university and study venue will monitor the implementation of the study and compliance with the ethical codes. Progress reports will be submitted regularly to the ethics committees for the auditing of the completeness, accuracy and timeliness of data collection as well as of the process related to enrolment, consent, eligibility and adherence to the protocol.

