#### Sample size

The sample size was calculated using the formula developed by Sugimoto et al. [42], incorporating the co-primary outcomes of this study: physical function and self-efficacy. Based on previous studies in arthroplasty, we expect the effect size of the intervention on self-efficacy to be 1.2 and that on the physical function to be 0.7 [20, 43]. The effect size ratio is approximately 1.7 (1.2/0.7). The correlation coefficient between these two outcomes was estimated to be 0.3 [44]. We set the attrition or nonresponse rate at 20% based on the evidence from the study of Walters et al. [45]. The present study requires a sample size of 84 in all (42 in each group) to achieve a power of 0.8 at a 0.025 level of alpha error.

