#### Primary outcomes

The primary outcomes are changes from baseline in self-efficacy and physical function at the completion of the intervention (T1). The intervention is based on the self-efficacy theory, aiming to improve patients’ physical function after surgery. These two outcomes may provide the most relevant and convincing evidence related to the aim of this study. The study results will be considered positive only if the intervention has an effect on both primary outcomes; thus, no adjustment for multiplicity will be conducted in data analysis [56].

Patients’ self-efficacy for rehabilitation will be measured using the Chinese version of the Self-Efficacy for Rehabilitation Outcome Scale (SER) [57]. The SER is sufficiently reliable and valid to detect patients’ self-efficacy for rehabilitation after hip or knee reconstructive/replacement surgeries [58]. It consists of 12 items that assess individuals’ beliefs in their ability to perform behaviours typical of physical rehabilitation, and each item is rated on an 11-point Likert scale from 0 indicating ‘I cannot do it’ to 10 indicating ‘certain I can do it’ [59]. Higher scores indicate greater self-efficacy.

Patients’ physical function will be measured using the Chinese version of the Hip Disability and Osteoarthritis Outcome Score Physical Function Short Form (HOOS-PS) for patients after THA and the Knee Injury and Osteoarthritis Outcome Score Physical Function Short Form (KOOS-PS) for patients after TKA [60, 61]. The HOOS-PS and KOOS-PS are valid for assessing patients’ perceptions of their hip or knee functions [62]. The HOOS-PS has five items, whereas the KOOS-PS has seven. Each item is graded from 0 indicating ‘no difficulty’ to 4 indicating ‘extreme difficulty’ [60, 61]. The raw sum score can be further converted in two directions: from no difficulty (0) to extreme difficulty (100) or from extreme difficulty (0) to no difficulty (100) [63]. To align with other scales in this study, such as the SER and EQ-5D-5L, the scores will be summed using the nomogram of worst (0) to best (100), with higher scores indicating better physical function. The minimal clinically important difference used in this study is 8 points for the HOOS-PS or KOOS-PS [64].

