Patients’ perceived HRQoL will be measured using the Chinese version of the EQ-5D-5L [68]. The EQ-5D-5L measures HRQoL on five dimensions: mobility, self-care, usual activities, pain/discomfort and anxiety/depression [69, 70]. In each dimension, respondents can indicate their health by ticking the box next to the most appropriate statement, and a digit number expressing the level selected will be produced [68]. Combining the digits for each dimension will produce a five-digit code that describes the patient’s health state. To compare the health state between the groups, the codes will be converted to index values according to the established value set for China [71]. The participants’ judgement of their health will be recorded with the EQ-VAS, where the endpoints are marked as 100 indicating ‘the best health you can imagine’ and 0 indicating ‘the worst health you can imagine’ [68].

The number of days when the participants use the WeChat programme and complete their rehabilitation tasks will be collected through reviewing rehabilitation diaries. The frequency of participants’ posts in the discussion forum on WeChat will be counted to understand online engagement. Complications and fall incidence that occur after randomisation will be investigated by additional questions on the questionnaire to provide information about the safety of using the app. With the individual’s consent, an interview will be conducted to discuss the benefits and barriers to using the app with participants in the experimental group.

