### Data analysis plan

IBM® SPSS Statistics 26.0 will be used to analyse the data [72]. The first author will perform data entry and analysis using participants’ identification codes. Categorical variables, such as gender, will be presented in frequencies and percentages. Continuous variables, such as age, will be presented as means with standard deviations or medians with interquartile ranges. Demographic characteristics and baseline variables will be compared between the two groups. Student’s *t*-tests will be used if the continuous data are normally distributed; otherwise, Wilcoxon rank-sum tests will be used. For categorical data, chi-square tests or Fisher exact tests will be conducted when chi-square testing is not valid. The effectiveness of the intervention will be analysed using the intention-to-treat principle [73]. The generalised estimating equation (GEE) model [74] will be used to compare the differential changes in the outcome variables between the groups across time points at a significance level of 0.05 (two-tailed). The GEE increases the efficiency of the estimates of the parameters in longitudinal trials by accounting for the within-subject correlations in repeated measurements [75]. This model is flexible to use as it relaxes the distribution assumptions of observed data and can accommodate missing data due to dropouts in RCTs [75, 76]. No imputation will be conducted if the proportion of missing data is less than 5% as the GEE can naturally integrate the missing data; otherwise, multiple imputations may be conducted [77].

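### Ending trial participation, not only the programme, after an event such as a dislocation or severe fall leaves outcome-related T1/T2 data uncollected and conflicts with the intention-to-treat aim

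*Protocol article*

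**What the plan says.** Four statements in the protocol article bear on this.

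- **Ethical consideration, the rule.** "The trial will be discontinued for a given participant if the participant withdraws consent, or if the participant develops a condition". The condition is one that a clinician diagnoses as "unsuitable for continuing the rehabilitation programme, such as joint dislocation and severe fall".
- **Ethical consideration, the next sentence.** "The conditions would be documented as adverse events and would be reported to the hospital for evaluation and treatment".
- **Data analysis plan.** "The effectiveness of the intervention will be analysed using the intention-to-treat principle". The model is a GEE, and on missing data the plan says: "No imputation will be conducted if the proportion of missing data is less than 5% as the GEE can naturally integrate the missing data". Above that threshold, multiple imputation is optional.
- **Secondary outcomes.** "Complications and fall incidence that occur after randomisation will be investigated by additional questions on the questionnaire", as the stated source of information on the safety of the app.

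The co-primary outcomes are changes from baseline to T1 (week 6). Under Outcome measures, the assessor may use the telephone when a participant cannot come to the hospital. Under Limitations of the study, all outcomes are described as self-reported.

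**The concern.** The trigger is that the *programme* has become unsuitable, but the consequence is that the *trial* ends for that person, in the same sentence and on the same footing as withdrawal of consent. The article nowhere says that T1 and T2 assessments continue. A participant who dislocates a joint or falls badly in week 3 would then contribute a baseline and nothing more.

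These are post-randomisation events closely tied to both co-primary outcomes, since someone with a dislocation can be expected to report poor function and low confidence. Following and analysing everyone as randomised is the point of intention-to-treat, and a rule that stops data collection because of such an event works against it. At stake are the T1 scores of some of the worst-off participants, harms that occur after the triggering event, and these participants' entries in the fall and complication questions. Data never collected cannot be recovered by any later analysis plan.

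**Working it through.** **1. The plan's own figure.** The point disputes no stated number, but the planned effect is the yardstick for any bias, so I checked it first. Inputs from Sample size: "we expect the effect size of the intervention on self-efficacy to be 1.2 and that on the physical function to be 0.7", correlation 0.3, power 0.8, alpha 0.025, attrition 20%.

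- Per group for the smaller effect, one-sided 0.025: n = 2(1.960 + 0.842)² / 0.7² = 32.04, so 33.
- Joint power for both outcomes at 33 per group with correlation 0.3: 0.811.
- Attrition: 33 / 0.8 = 41.25, so 42 per group and 84 in all. This reproduces the plan.

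**2. The statements side by side.**

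| Question | What the article provides |
|---|---|
| What stops? | The trial, for that participant |
| T1/T2 assessment afterwards? | Not provided for |
| Triggering event recorded? | Yes, as an adverse event |
| Later harms and questionnaire entries? | Not provided for |
| Excluded from the analysis set? | Not said |
| Analysis principle | Intention-to-treat |

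By contrast, under Concomitant rehabilitation and medications the article states that participants sent to extra in-person sessions stay in the analysis. The discontinuation rule has no matching sentence.

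**3. Size of the bias, under assumptions.** Let f be the share of an arm lost and D the deficit, in SD, of those lost relative to those retained. The full-arm mean is the retained mean minus f × D, so with a common D the bias in the between-arm difference is (f_exp − f_con) × D. The article gives neither f nor D. The values below are illustrations with 42 per arm.

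| Lost, experimental v control | Bias, D = 1 SD | Bias, D = 2 SD |
|---|---|---|
| 1 v 1 | 0 | 0 |
| 2 v 1 | 1/42 × 1 = 0.024 | 1/42 × 2 = 0.048 |
| 4 v 1 | 3/42 × 1 = 0.071 | 3/42 × 2 = 0.143 |
| 4 v 4 | 0 | 0 |

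Against 0.7 SD this runs from 0.024 / 0.7 = 3% to 0.143 / 0.7 = 20%. If the losses fall mainly in the control arm, the same sizes apply with the opposite sign, against the app. Only events before T1 touch the co-primary outcomes; later ones affect T2.

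**4. Whether the analysis repairs it.**

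- Unweighted GEE needs data missing completely at random, and loss triggered by a dislocation or severe fall is not that.
- Below 5% missing nothing is imputed. Four participants of 84 is 4.8%, so with no other missing data even four such losses would go unimputed. The 2 v 1 case is 3/84 = 3.6%. The 4 v 1 case is 5/84 = 6.0%, where imputation becomes possible but not required.
- Standard multiple imputation assumes missing at random. For an event between baseline and T1, the only observed outcomes predate it, and the participants removed under the rule supply no post-event scores for the imputation model to learn from. Imputed values would resemble those of people who had no such event.

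**The case against.** The case on the other side is substantial.

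- **The harms are not erased.** A reader might infer that the most serious events vanish from the safety data. The text does not support this, because the sentence after the rule documents the triggering conditions as adverse events. Only later harms and the questionnaire entries are exposed. This objection stands.
- **Intention-to-treat is not abandoned.** A reader might infer that these participants are dropped from the analysis. Nothing says so: their baseline, and T1 if the event comes later, can stay in the GEE under the allocated arm. What arises is a missing-data problem that works against the aim. This stands too.
- **Nothing shows that the app benefits.** The exercises are the same in both arms, the control arm also follows a six-week programme, so the rule can apply to both, and patients with major postoperative complications are excluded. An imbalance is possible, because the experimental arm has weekly messages and a forum with clinicians, so an event may be noticed more readily there. That is inference, and the documents do not establish a direction.
- **The wording may be loose, and the article is condensed.** The programme may have been meant, and the full protocol is not shown. But this is not a detail left out. The article states a rule, and couples it with withdrawal of consent. A sensitivity analysis in an unseen analysis plan could explore the loss but could not restore the scores. This objection lowers the certainty about intent, not the need to reconcile the text.

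**Conclusion.** The point holds in a limited form. As written, the discontinuation rule ends trial participation for an outcome-related reason arising after randomisation, and no T1 or T2 assessment is provided for afterwards. This conflicts with the intention-to-treat aim, and the planned analysis does not correct the resulting loss.

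The size and direction of any bias are unknown. It is zero with equal losses and equal deficits in the two arms, and about 0.02 to 0.14 SD in the illustrated range, compared with the planned 0.7 SD for physical function. Those figures rest entirely on assumed losses and an assumed 1 to 2 SD deficit. The likely number of participants is small; the reason to act is that the information cannot be obtained later.

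**What to change.** Reconcile Ethical consideration, Data analysis plan and the safety questions under Secondary outcomes, as follows.

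- Distinguish discontinuation of the rehabilitation programme from withdrawal from the trial. When the programme is stopped is a clinical decision and is not judged here.
- State that T1 and T2 outcome and safety assessments continue after programme discontinuation, by telephone if needed, unless the participant withdraws consent to follow-up.
- State that all randomised participants are analysed in their allocated group.
- Record programme discontinuation and its reason separately from trial withdrawal.

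The extra data collection is a few telephone assessments, using a route that the article already allows and outcomes that are all self-reported. The administrative cost is larger. Under Modification of the protocol, a substantive change needs a formal written amendment, approval by both ethics committees, a register update, notification of participants and consent to the modified study. Trial status reports 48 participants already recruited, so the change should be made promptly.

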### Modification of the protocol

Any modification of the protocol will be discussed and determined by all research team members. Substantive amendments that may impact the conduct of the study or the ethical rigour of the study, such as changes of objectives, eligibility criteria, study procedure and data analysis, will require a formal written modification to the protocol. The protocol will be identified by a unique version number and date. Such amendments would be approved by the ethics committee of the university and the study venue before they are implemented. The modification will be updated on the trial register and notified to participants after it has been approved. Consent to participate in the modified study will be required. Other amendments, such as minor corrections and clarifications that would not affect the conduct of the study, will be documented as a memorandum.

## Discussion

The present study will investigate the effectiveness of a theory-based mobile app rehabilitation programme regarding self-efficacy, physical function, pain, depression, anxiety and HRQoL among patients after THA or TKA. To the best of our knowledge, this is the first trial conducted in China about mobile app-based rehabilitation after arthroplasty that incorporated a self-efficacy and learning theoretical framework. The results will add robust evidence on the effectiveness of the rehabilitation services delivered via mobile apps and will provide insight into the application of these theories in telehealth. The evidence from this study may contribute to clinical recommendations and future research about mobile app-based rehabilitation. If the findings are positive, the evidence from this study will support the provision of mobile app-based rehabilitation to patients after THA or TKA, which might increase the accessibility of rehabilitation services [18] to benefit patients who are not able to attend face-to-face rehabilitation. With the support of mobile apps, patients’ adherence to rehabilitation might be increased as they could obtain support, such as readily accessible information and reminders [78].

The primary outcomes of this study are changes in self-efficacy and physical function because the mobile app rehabilitation programme targets enhancing patients’ self-efficacy for rehabilitation and improving their physical function. The results will provide evidence about patients’ self-efficacy in telerehabilitation after arthroplasty, which has seldom been reported in previous studies. A previous study reported that telephone follow-up significantly improved patients’ general self-efficacy one month after TKA [79], but patients’ self-efficacy in mobile app-based rehabilitation remains unknown. Self-efficacy for rehabilitation plays an important role in the interpretation of the effectiveness of rehabilitation, and it is suggested to be included in the outcome measures [11]. As patients’ recovery is represented by multidimensional factors involving their physical, mental, social and vocational abilities [80], secondary outcomes, including pain, depression, anxiety and HRQoL, will also be assessed in the present study to examine the changes in patients’ symptoms, emotional recovery and quality of life. These outcomes will provide a comprehensive understanding of the effect of mobile app-based rehabilitation after arthroplasty as well as the opportunity to explore the interaction between physical and psychological outcomes.

### Limitations of the study

Given the nature of the intervention, double-blinding is not possible. However, the outcome assessor will be blinded in this study. To reduce the confounding variables caused by different rehabilitation protocols in different hospitals, the present study will be a single-centre trial. This might reduce the generalisation of the findings to a broader population. The outcomes will be assessed using self-reported measures as it is difficult to conduct objective measures after hospital discharge, especially for patients who live in other cities or rural areas outside Shanghai. Due to the time constraints of a doctoral programme, of which this study is part, the follow-up period is limited to 10 weeks. Future studies could include longer follow-up periods, such as 6 or 12 months postoperatively, to assess the long-term effectiveness of mobile app rehabilitation programmes.

### Trial status

Participant recruitment commenced on May 25, 2021 (protocol version 3, dated April 1, 2021). Up to now, 48 participants have been recruited. Recruitment is expected to be completed in October 2021. Findings from this study will be published in peer-reviewed journals and presented at conferences.

## Conclusion

This study will contribute to the knowledge about the effectiveness of mobile app-based rehabilitation among patients after THA or TKA. If the findings are positive, they will support the implementation of mobile app-based rehabilitation in THA or TKA, which might increase the accessibility of rehabilitation services and patient adherence to rehabilitation.

## Data Availability

The study protocol will be published in the journal and provided on the Australian New Zealand Clinical Trials Registry. The unidentified datasets generated from this study will be available from the corresponding author upon reasonable request.

## Abbreviations

THA: Total hip arthroplasty
TKA: Total knee arthroplasty
HRQoL: Health-related quality of life
app: Application
RCT: Randomised controlled trials
SPIRIT: Standard Protocol Items: Recommendations for Interventional Trials
HOOS-PS: Hip Disability and Osteoarthritis Outcome Score Physical Function Short Form
KOOS-PS: Knee Injury and Osteoarthritis Outcome Score Physical Function Short Form
SER: Self-Efficacy for Rehabilitation Outcome Scale
NRS: Numeric Rating Scale
HADS: Hospital Anxiety and Depression Scale
GEE: Generalised estimating equation
